#### Randomization and blinding

Recipients with signed informed consent meeting all inclusion criteria and without any exclusion criteria will undergo transplantation with grafts that have been randomized to Custodiol® or Custodiol-N in a blinded manner. Grafts are randomized in a 1:1 ratio to receive either Custodiol® or Custodiol-N. After randomization, the randomized solution will be prepared for treatment at the donor site. Study medication will not be blinded for the investigator. Randomization will be performed using the web-based randomization service “Randomizer for Clinical Trials” developed at the Institute for Medical Informatics, Statistics and Documentation, Medical University of Graz, Austria.

#### Packaging and labelling

Trial medication will be provided by the sponsor as 1-litre bags (3 litres for one patient) and the appropriate amount of lyophilisate per bag to the distributing pharmacy. Packages will be opaque and labelled with either “Custodiol®” or “Custodiol-N” in an unblinded fashion and with the study title, EudraCT number and “Zur klinischen Prüfung bestimmt”, according to the Directive 2001/20/EC of the European Parliament. Each bag will be labelled in the same way. To ensure allocation concealment, clinical monitors will check that unused medication packages have not been opened.

### Study procedure

The trial will begin when history taking has shown that the criteria for inclusion in the trial have been met (performed by the study team of transplant surgeons), and when the patient has been fully informed regarding the objective of the study, the trial product, the risks and the insurance cover, and when the signed declaration of consent is available. Allocation principles are shown in Fig. 1.

**Fig. 1 Fig1:**
[figure not shown]
Consolidated Standards of Reporting Trials (CONSORT) flowchart of randomization. AUT Austria, ET Eurotransplant, HTK histidine-tryptophan-ketoglutarate, MELD investigational medicine product

#### Organ perfusion technique

The perfusion of all abdominal organs with cold (2–8°C) Custodiol® will be performed according to the standard procedure. Briefly, after mobilization and appropriate preparation of intra-abdominal organs and blood vessels and clamping of the aorta above the superior mesenteric artery, perfusion with Custodiol® is started via the infrarenal aorta. The duration of perfusion is usually 10–15 min. During perfusion, the abdominal cavity is cooled with cold physiological NaCl solution. Cold storage of grafts must be performed in the solution used for perfusion of the donor.

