**Methods:**

Patients undergoing kidney transplantation (*n* = 412) (including approximately 30 combined kidney–pancreas) or liver transplantation (*n* = 202) receive grafts that have been cold stored in either Custodiol® or Custodiol-N to demonstrate noninferiority of Custodiol-N regarding both graft function and graft injury after transplantation.

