### Study medication

#### Treatment assignment

The reported organ donors are allocated according to the Eurotransplant guidelines without influence from the study. Only organs allocated to a patient who has signed the informed consent will be randomized.

Multiorgan donation is performed according to institutional guidelines. Organ perfusion is performed using Custodiol® as the standard preservation solution. Subsequently, organs allocated to a study centre with patients who have signed the informed consent will be randomized to either study medication. In case of simultaneous transplantation of the kidney and pancreas, both organs will be randomized together for the same study arm.

After randomization, back table perfusion with study medications will be performed via the renal artery for the kidney, the hepatic artery as well as the portal vein for the liver, and the mesenteric artery and portal vein for the pancreas using approximately 250–1000 ml of study medication per organ (Custodiol® or Custodiol-N). Subsequently, the grafts will be stored in 1000 ml of the study medication. The allocated study medication is provided to the recipient site. Before transplantation, back table perfusion using approximately 250–1000 ml of the study medication will be optionally performed.

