#### Analysis sets

All organs randomized and implanted or with an attempt to implant will be included in the analysis according to the randomized treatment group. Organs randomized but not implanted will count as screening failures.

All patients treated according to the study protocol will be included in the per-protocol set. A list of protocol deviations sufficient to exclude patients from this set will be compiled by the sponsor, the main investigator and the biostatistician before analysis starts. The primary analysis will be performed on the per-protocol set.

All tests of the primary criteria with respect to the liver and kidney would have to successfully reject the null hypothesis to support a favourable result with respect to Custodiol-N. Null hypothesis tests will be repeated for intention-to-treat sets.

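### The storage rule under Organ perfusion technique would put grafts randomized to Custodiol-N into the control solution, against the Treatment assignment section

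*Protocol article*

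**What the plan says.** Two sections of the protocol article fix the storage solution, and they disagree.

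- **Treatment assignment** (under Study medication) gives the sequence for the trial. For the donor: "Organ perfusion is performed using Custodiol® as the standard preservation solution". Organs are randomized after that and flushed on the back table with 250–1000 ml of the randomized solution. Then: "Subsequently, the grafts will be stored in 1000 ml of the study medication". A further flush may follow at the recipient site: "Before transplantation, back table perfusion using approximately 250–1000 ml of the study medication will be optionally performed".
- **Organ perfusion technique** (under Study procedure) describes aortic perfusion of all abdominal organs with cold Custodiol®, without distinguishing arms, and ends: "Cold storage of grafts must be performed in the solution used for perfusion of the donor".

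Three other places bear on the point.

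- The **abstract (Methods)** says that patients "receive grafts that have been cold stored in either Custodiol® or Custodiol-N".
- **Packaging and labelling** provides 3 litres of trial medication per patient, in 1-litre bags.
- **Analysis sets** makes the per-protocol set primary, repeats the tests by intention to treat, and leaves the grounds for exclusion open: "A list of protocol deviations sufficient to exclude patients from this set will be compiled by the sponsor", together with the main investigator and the biostatistician, before analysis starts.

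**The concern.** The solution used to perfuse the donor is Custodiol® in both arms, because randomization comes later. A mandatory rule that ties storage to that solution therefore puts Custodiol-N grafts into the comparator. Control-arm grafts are unaffected, since both rules give them Custodiol®.

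Two things are at stake.

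1. **The contrast.** Cold storage is the exposure the trial compares. A Custodiol-N graft handled under the Organ perfusion technique rule would meet its allocated solution only in the flushes. The arms become more alike, and if Custodiol-N is truly worse, that makes a false claim of noninferiority easier.
2. **Compliance.** A Custodiol-N graft stored in Custodiol® deviates from one section and complies with the other. Because the primary analysis is per protocol, membership of the primary set depends on which sentence is believed.

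**Working it through.** **Step 1. What each rule implies**

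| | Donor perfusion | Storage, Custodiol® arm | Storage, Custodiol-N arm |
|---|---|---|---|
| Treatment assignment | Custodiol® | Custodiol® | Custodiol-N |
| Organ perfusion technique | Custodiol® | Custodiol® | Custodiol® |

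Two readings could remove the conflict, and neither is supported. Donor perfusion could be taken to mean the back table flush. However, the sentence closes a paragraph solely about aortic perfusion, while the flush is described elsewhere, organ by organ, through each organ's own vessels. The sentence could also be meant only for the time before randomization, but it states no such limit.

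**Step 2. Which rule is intended**

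Study medication needed per organ, at most:

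- Treatment assignment: 1000 ml flush + 1000 ml storage + 1000 ml optional flush = 3000 ml.
- Organ perfusion technique: 1000 + 0 + 1000 = 2000 ml.

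The supply is 3 litres per patient. It matches the first rule, as does the abstract.

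**Step 3. Illustration of the effect on error rates**

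Inputs from the Sample size determination section:

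- Kidney: 412 patients (206 per arm), control rate of delayed graft function 30%, margin 15 percentage points, one-sided alpha 0.025, Farrington-Manning test.
- Liver: 202 patients (101 per arm), coefficient of variation 0.5, margin ratio 1.25, t test on lognormal data.

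Assumptions, not in the documents:

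- f is the share of Custodiol-N grafts stored in Custodiol®, set at 10%, 25% and 50%.
- r is the share of the harm that a mis-stored graft keeps.
- Mis-stored grafts stay in the analysis set.

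*Kidney*, with Custodiol-N truly at the margin (45% against 30%). The observed test-arm rate is

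0.45(1 − f) + (0.30 + 0.15r)f.

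For example, f = 0.25 and r = 0 gives 0.3375 + 0.075 = 0.4125. The probability of declaring noninferiority, by exact binomial enumeration, is:

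| f | Rate, r = 0 | P, r = 0 | Rate, r = 0.5 | P, r = 0.5 |
|---|---|---|---|---|
| 0 | 0.450 | 0.025 | 0.450 | 0.025 |
| 0.10 | 0.435 | 0.050 | 0.4425 | 0.036 |
| 0.25 | 0.4125 | 0.125 | 0.431 | 0.059 |
| 0.50 | 0.375 | 0.372 | 0.4125 | 0.125 |

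*Trial level.* The article requires both organs to succeed: "All tests of the primary criteria with respect to the liver and kidney would have to successfully reject the null hypothesis". On the log scale the liver SD is √ln(1 + 0.5²) = √ln 1.25 = 0.472. If the liver is truly equivalent (ratio 1.0), its power with 101 per arm is 0.916. If the liver is at its margin, the diluted ratio is 1.25^(1 − f). The joint probability is kidney (r = 0) × liver, assuming independence:

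| f | Liver at margin, liver test alone | Joint, liver equivalent | Joint, liver at margin |
|---|---|---|---|
| 0 | 0.025 | 0.023 | 0.0006 |
| 0.10 | 0.052 | 0.046 | 0.003 |
| 0.25 | 0.130 | 0.114 | 0.016 |
| 0.50 | 0.386 | 0.341 | 0.14 |

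**The case against.** The strongest reply is that the article largely resolves its own conflict. Treatment assignment is the trial-specific section and gives the whole sequence. The randomized solution is prepared at the donor site and supplied in labelled bags with a litre for storage, and the abstract defines the comparison by storage. A team at one of two centres running a trial of storage solutions is unlikely to set that litre aside because of a closing sentence on aortic technique. This stands as an argument that harm is unlikely. It does not make the sentence right: it is a mandatory instruction about the intervention itself.

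Three further points are fair.

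- **Size.** Nothing in the documents supports any particular share of mis-stored grafts. The larger figures also assume true harm at the margin, no exclusion from the analysis set, and no harm in grafts that were still flushed with Custodiol-N. With half the harm kept, 10% mis-storage gives 3.6% rather than 2.5%. With both organs at the margin, the joint rate stays below 2.5% at 10% and 25%.
- **Direction.** Dilution favours noninferiority only if Custodiol-N is worse. If the solutions are equal, nothing changes. If Custodiol-N is better, say 25% against 30% delayed graft function (assumed), 50% mis-storage lowers the chance of kidney success slightly, from 99.5% to 97.6%.
- **Deviation list.** The list is still to be written, and its absence from the article is no fault. If mis-storage is listed, the primary set is protected and only the intention-to-treat repeat is diluted.

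These points limit the consequence. They leave the contradiction in place.

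**Conclusion.** The concern holds. As written, the last sentence of Organ perfusion technique is wrong for the test arm and contradicts both Treatment assignment and the abstract. The supply figure shows that Treatment assignment is very probably the intended rule. This part rests on the text alone, with high confidence.

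The size of any effect cannot be derived from the documents, because it depends on how many teams would follow the wrong sentence and whether those grafts would be excluded. Under the stated assumptions, inflation of the kidney error rate runs from slight (3.6% at 10% mis-storage with half the harm kept) to severe (37% at 50% with none kept). These figures illustrate the risk and are not a forecast. The point should be fixed: the sentence governs the exposure under test, and correcting it costs almost nothing.

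**What to change.** Replace the last sentence of Organ perfusion technique with: *After randomization and back table perfusion, grafts are cold stored in the allocated study medication (Custodiol® or Custodiol-N).* If the old sentence was meant for the interval before randomization, add that organs are held in Custodiol® until randomization only.

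In the list of protocol deviations already planned under Analysis sets, name storage in any solution other than the allocated one as a deviation that excludes the graft from the per-protocol set.

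The cost is one replaced sentence and one list entry. Sample size, supply and the intended procedure do not change.

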### Kidney

#### Screening of donor and graft status

The screening visit includes a check of the inclusion and exclusion criteria, assessment of demographic data (age and gender), the clinical status (sodium, serum creatinine, urea, catecholamines (yes/no)), mechanical or medicamentous cardiopulmonary resuscitation of the donor (yes/no), the graft damage (biopsy after reperfusion, damage to vessels, laceration), and duration of cold ischemia (Fig. 2).

**Fig. 2 Fig2:**
[figure not shown]
Template of content for the schedule of enrolment, interventions and assessments. SPIRIT figure for kidney transplantation. MDRD modification of diet in renal disease

#### Screening of the recipient

The screening visit includes a check of the inclusion and exclusion criteria (to test female patients ≤55 years for pregnancy), assessment of demographic data (age and gender) of the recipient, and informed consent by the study team. Within 24 h before transplantation, the recipients’ routine laboratory results (serum creatinine, creatinine MDRD clearance and urea) are recorded. Diuresis is also assessed. Additionally, the occurrence of adverse advents and concomitant medication will be recorded. Events compromising the blinding of the patient will be recorded as protocol deviations.

#### Follow-up

Follow-up will be performed daily up to day 7, and at postoperative days 30 (±3 days) and 90 (±7 days). These follow-up visits assess the recipient’s clinical status (American Society of Anesthesiologists (ASA) classification), episodes of dialysis, the recipients’ routine laboratory results (serum creatinine, creatinine MDRD clearance, urea) and the diuresis per hour (up to 7 days). Haemoglobin will be analysed on day 30 and after 90 days. Additionally, the occurrence of biopsy-proven rejections (according to Banff criteria) and adverse advents are recorded. Relevant concomitant medication (catecholamines, immunosuppression, anti-infectives, antihypertensives, antiarrhythmics, and diuretics) will be recorded in detail up to day 7 of follow-up and at days 30 and 90 after transplantation as ‘yes’ or ‘no’ only.

### Liver

#### Screening of donor and graft status

The screening visit includes a check of the inclusion and exclusion criteria, assessment of demographic data (age and gender) and the clinical status (sodium, AST, ALT, LDH, bilirubin, catecholamines (yes/no), reanimation (yes/no)) of the donor, the graft damage (biopsy after reperfusion, damage to vessels, laceration), biopsy (steatosis (micro-/macrovesicular)), inflammatory changes, fibrosis and duration of cold ischemia (Fig. 3).

**Fig. 3 Fig3:**
[figure not shown]
Template of content for the schedule of enrolment, interventions and assessments. SPIRIT figure for liver transplantation. ALT alanine aminotransferase, ASA American Society of Anesthesiologists, AST Aspartate aminotransferase, LDH lactate dehydrogenase, MELD model for end-stage liver disease, PT prothrombin time

#### Screening of the recipient

The screening visit includes a check of the inclusion and exclusion criteria (to test female patients ≤55 years for pregnancy), assessment of demographic data (age and gender) of the recipient, and informed consent. Within 24 h before transplantation, the recipients’ clinical status (calculated model for end-stage liver disease score) and the recipients’ routine laboratory results (serum bilirubin, AST, ALT, LDH, total albumin) are assessed. Additionally, the occurrence of adverse advents and concomitant medication will be recorded. Events compromising the blinding of the patient will be recorded as protocol deviations.

#### Follow-up

Follow-up will be performed daily up to day 7, and at postoperative days 30 (±3 days) and 90 (±7 days). These follow-up visits assess the recipient’s clinical status (ASA classification), biopsy-proven rejection episodes (according to Banff criteria), the recipient’s routine laboratory results (serum bilirubin, AST, ALT (a minimum of two times per day between days 1–7), LDH, total albumin) and prothrombin time after 30 days and 3 months, and biliary complications (number of episodes of cholestasis, therapy for cholangitis, episodes of biliary leakage and intrahepatic and/or extrahepatic biliary strictures). Additionally, the occurrence of any adverse advents will be recorded. Relevant concomitant medication (catecholamines, immunosuppression, anti-infectives, antihypertensives, antiarrhythmics, and diuretics) will be recorded in detail up to day 7 of follow-up and at days 30 and 90 after transplantation as ‘yes’ or ‘no’ only. Graft survival will be recorded, and parenteral nutrition will be checked.

### Combined kidney–pancreas

#### Screening of donor and graft status

The screening visit includes a check of the inclusion and exclusion criteria, assessment of demographic data (age and sex), the clinical status (sodium, serum creatinine, urea, catecholamines (yes/no), reanimation (yes/no) of the donor) and the graft damage (kidney biopsy, damage to vessels, laceration). Additionally, the donor status according to the Pancreas Allocation Suitability Score and the duration of cold ischemia for the pancreas and kidney are recorded (Fig. 4).

**Fig. 4 Fig4:**
[figure not shown]
Template of content for the schedule of enrolment, interventions and assessments. SPIRIT figure for pancreatic transplantation. MDRD modification of diet in renal disease, PASS Pancreas Allocation Suitability Score

#### Screening of the recipient

The screening of the recipient includes a check of the inclusion and exclusion criteria (to test female patients ≤55 years for pregnancy), assessment of demographic data (age and gender) of the recipient, and informed consent. Within 24 h before transplantation, in addition to the recipient’s clinical status (ASA classification) and routine laboratory results (serum creatinine, creatinine MDRD clearance, urea) the recipient’s C-reactive protein is recorded. Diuresis is also assessed.

#### Follow-up

Follow-up will be performed daily up to day 7, and at postoperative days 30 (±3 days) and 90 (±7 days). These follow-up visits assess the recipient’s clinical status (ASA classification), episodes of dialysis, the recipient’s routine laboratory results (serum creatinine, creatinine MDRD clearance, urea) and the diuresis per hour (up to 7 days). Haemoglobin will be analysed on day 30 and after 90 days. Additionally, the occurrence of biopsy-proven rejections (according to Banff criteria) and adverse advents are recorded. Relevant concomitant medication (catecholamines, immunosuppressors, anti-infectives, antihypertensives, antiarrhythmics, diuretics) will be recorded in detail up to day 7 of follow-up and at days 30 and 90 after transplantation as ‘yes’ or ‘no’ only. Follow-up visits at day 1, day 3, day 30 and day 90 will assess pancreatic complications such as graft pancreatitis and anastomotic leak and vascular complications (thrombosis, stenosis, bleeding). The routine laboratory findings (lipase, α-amylase and C-reactive protein) are measured on day 1 and 3 days after transplantation. Further insulin requirements on days 3 and 30 (±3 days) and after 90 days will be assessed. The glycated haemoglobin level and C-peptide level are measured at days 30 and 90 after transplantation. Fasting glucose will also be documented 90 days after transplantation. Adverse events are documented up to day 90. Pancreas-relevant concomitant medication (insulin/antidiabetics) will be documented in detail up to day 3 of follow-up and at days 30 and 90 after transplantation as ‘yes’ or ‘no’ only. Graft survival will be recorded.

### Data management

#### Data collection and handling

All information required by the protocol and collected during the trial must be entered by the investigator, or a designated representative, in the electronic case report form (eCRF). Each patient will be assigned a site number and a site-specific screening number reflecting the chronological order of screening. Any link of the site number to a patient’s identity will be kept confidential at the study site. Each donor organ will be identified by a randomization code while the type of organ is conveyed implicitly; right and left kidneys will be identified. The investigator, or a designated representative, should complete the eCRF pages as soon as possible after the information is collected, preferably on the same day as a trial participant is seen for an examination, treatment, or any other trial procedure. Any pending entries must be completed immediately after the final examination. Explanation should be given for all missing data.

Data management is accomplished according to the appropriate standard operating procedures valid in the Institute for Medical Informatics, Statistics and Documentation, Medical University Graz, Austria.

After completion of the query process, the database will be closed and exported into the statistical evaluation system for analysis.

#### Storage and archiving of data

All important trial documents (e.g. the eCRF) will be archived by the sponsor for at least 10 years after the trial termination.

The investigator(s) will archive all trial data (source data and the Investigator Site File including the participant identification list and relevant correspondence) according to section 4.9 of the International Council for Harmonisation (ICH) Consolidated Guidelines on Good Clinical Practice (GCP) (E6) and according to local law or regulations [28].

### Statistical analysis

#### Sample size determination

Sample sizes have been calculated for the kidney and liver. The trial will stop once both sample sizes have been reached.

Very few patients are expected to be lost to follow-up as they will be under close clinical observation. Also, a patient’s active termination from the study is expected to happen very rarely as very few procedures will be study-specific and personal data will be used for transplantation registers anyway. Therefore, no additional patients are planned to be enrolled to make up for attrition effects.

